## Discussion

To explain behavior change, many behavioral change theories, like the health belief model [45], socio-cognitive theory [46], and trans-theoretical framework [47], are being used, focusing upon different factors. The current study will consider the trans-theoretical framework to address the change in behavior towards tobacco cessation after providing an intervention. This framework is used for following reasons: firstly, this helps to assess an individual's readiness to act on a new healthier behavior. Secondly, it provides strategies or processes of change to guide the individual. Third, this framework will emphasize the importance of tobacco users' motivation and self-efficacy while considering the barriers to change and cues to action. Studies worldwide using trans-theoretical model (TTM) to track tobacco use behavior have established its validity and reliability across various settings [48–52]. Furthermore, this framework will help clinicians track tobacco users' movement from one stage to the next stage [53].

The tobacco cessation intervention (TCI) has variably shown the effectiveness and efficacy of reducing ill health and increasing quality-adjusted life years (QALY). A systematic review [54] concluded the cost-effectiveness of intensive over brief tobacco cessation intervention with 960 and 280 discounted cumulative number of QALYs per year respectively gained in the two interventions. Further studies documented intensive tobacco cessation intervention in reducing ill-health, morbidity, and mortality compared to brief intervention [55]. As no evidence could be reported on the comparative effectiveness of intensive over the brief intervention for tobacco cessation in the Indian hospital setting, the results of current study will provide quality evidence to replicate the protocol in similar settings across the globe.

Despite the strong evidence about the effectiveness of tobacco cessation intervention in community settings, its implementation by health professionals in tertiary care has still not been explored. Tobacco-related diseases are one of the main reasons for all general hospital admissions [56]. During hospital stays, these patients should be advised to stop tobacco use because this decision has been related to reductions in morbidity and mortality [57]. Although many healthcare delivery centers restrict or prohibit patients from tobacco use to protect other patients and staff from the effects of passive smoking, this tobacco-free environment may provide an opportunity for hospitalized patients to attempt abstaining from its use.

Nevertheless, the use of intervention for cessation has been frequently ignored by health professionals in hospitalized populations and often discharge patients from tertiary care without sufficiently addressing opportunities for tobacco prevention [58, 59]. For this reason, providing (or at least initiating) tobacco dependence treatments in hospitals may be an effective preventive health strategy [60, 61]. To our knowledge, no study in an Indian setting has investigated the effects of tobacco-cessation intervention in a subset of patients admitted in a tertiary healthcare delivery center. Thus, the study will build evidence on the effectiveness of interventions in such settings and advocate for a tailored intervention.

Most of the existing studies relied on questionnaire methods such as Russell Standard for self-reporting abstinence rather than biochemical verification to measure tobacco use status. The biochemical verification shall increase rigor and validity compared to self-reported tobacco abstinence. However, it also has limitations, including the inability to confirm long-term abstinence, implementation challenges, and high performance cost.

The study has several strengths and endeavors to strengthen the theoretical framework for tobacco cessation interventions. Firstly, this will be the first comprehensive study from India conducted in tertiary care setting comparing intensive with brief intervention for tobacco cessation. Secondly, it will use a holistically designed intervention developed after obtaining all stakeholders’ views, including tobacco users. Thirdly, it shall examine the effect of tobacco cessation intervention after 1, 3, and 6 months of providing intervention, which will provide an opportunity to evaluate long-term treatment effects on tobacco abstinence. At last, verification of quitting status with cotinine assessment will strengthen the validation of outcomes. There are few possible limitations of the study. First, the possibility of missing data throughout the follow-up period cannot be ignored, which shall influence the validity and internal reliability of the results. However, this is a frequent phenomenon of any long-term trial involving tobacco cessation. Second, the results may not be generalized for the general population as the participants will be from the hospital settings in the study. Moreover, the effect of secondhand smoke (SHS) in the measurement could not be ascertained. Social context in tobacco has been widely cited as integral to understanding why, how, where, and with whom people use tobacco, along with and the non-random social distribution of tobacco use. Although the need to incorporate the social context has now been recognized by many of the disciplines involved in tobacco control research, its measurement was out of scope of the study.

The current study has few policy and programmatic implications. As the intervention package for tobacco cessation has been developed through a formative research, evidence shall inform and provide insights on its acceptability and feasibility at a larger scale across several centers and countries. With limited use of health system resources such as healthcare personnel (counselors) and space, the findings of this study will provide direction to policy makers, implementers, and educators for implementing the intervention in their settings. Since research in this area is in its infancy in LMIC and MICs, therefore, this will provide an impetus for researchers working on tobacco cessation to generate new evidence in real-time practice. 

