	(Motivational videos) Videos based on real life stories of patients with tobacco use history will educate and sensitize patients and care givers on harmful effects of tobacco and motivate patients to quit	3–5 min/once during first contact/researcher	Technology including mobile phones, the internet, and social media platforms, can increase access to care by extending the work of counselors and overcoming the geographical barriers. These supports can increase the likelihood of adults quitting compared with no intervention and can be a cost-effective adjunct to other treatments [39]
	(Patient information leaflet (PIL)) Patient information leaflet will be based on specific characteristics or concerns of tobacco users and include written material aiming to educate patients about the disease, ill effects of using tobacco on health, benefits of quitting and how to resist cravings and avoid relapse	Once at first contact/researcher	Providing self-help materials (primarily print-based) tailored to the individual patient (that is, beyond a brochure that simply describes the health effects of tobacco use and benefits of cessation) is effective in improving tobacco abstinence [40]
**Intensive**	(Telephone counseling) Counseling through regular telephone follow-up will provide support and encouragement to individuals who uses tobacco and want to quit or individuals who have recently quit	05–15 min/five times at < 1, 4, 6, 9, and 12 weeks in 3 months after enrolment/researcher	Telephone-based access to counseling and smoking cessation resources increases cessation rates. The majority of helplines provide access to individual counseling; the greatest amount of counselor contact, the greater the likelihood of successful cessation [41]
	(Text messages using SMS) Messages will include short text based on the current stage of behavior as per trans-theoretical model for their motivation and support regarding tobacco cessation and maintaining quit status	Bi-weekly for 3 months/researcher	Technology, including mobile phones, the internet, and social media platforms, has the power to increase access to care by extending the work of counselors and overcoming geographical barriers. These supports can increase the likelihood of adults quitting compared with no intervention and can be a cost-effective adjunct to other treatments [39]

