### Data collection

After fulfilling the inclusion criteria and seeking written consent, the researcher will collect data from tobacco users enrolled in the study. Baseline and end of follow-up (6 months) of intervention assessment will include assessment of tobacco use (daily tobacco consumption, age of initiation, quit attempt, treatment sought for cessation (if any)); knowledge, attitude, and practices about tobacco use.

The assessment of motivation to quit tobacco will be undertaken using Readiness to Change questionnaire [42] (RCQ), nicotine dependence using FTND scale [43], and stages of behavior change using a trans-theoretical model of behavior change at each follow-up (0, 1, 3, 6) months. The self-reporting assessment for 7-day point prevalence and continuous tobacco abstinence will also be done at each (0, 1, 3, 6) follow-up month. In addition, a urine sample will be collected at the last follow-up (6 months of intervention) to confirm the cotinine presence biochemically (Table 2).

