### Outcome measures

#### Primary outcome

Validated 7-day point prevalence tobacco abstinence at 6 months (last follow-up) measurement using urinary cotinine

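### Six-month continuous abstinence is accepted on self-report alone, although urine cotinine is measured at the same visit

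*Protocol article*

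**What the plan says.** All references are to the protocol article.

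- **Primary outcome:** "Validated 7-day point prevalence tobacco abstinence at 6 months (last follow-up) measurement using urinary cotinine".
- **Data collection:** "a urine sample will be collected at the last follow-up (6 months of intervention) to confirm the cotinine presence biochemically". No earlier urine sample is mentioned. On the reported measures the same section says: "The self-reporting assessment for 7-day point prevalence and continuous tobacco abstinence will also be done at each" assessment month (0, 1, 3 and 6).
- **Secondary outcomes and Table 3:** continuous abstinence at 1, 3 and 6 months is listed as self-reported. Only the validated 7-day outcome has cotinine as its measurement.
- **Blinding:** the study is open-label, and the researcher who delivers the intervention also assesses the outcome, knowing the arm.
- **Intervention/treatment arm, Table 1:** intensive-arm calls are made "five times at < 1, 4, 6, 9, and 12 weeks in 3 months after enrolment", and text messages go out "Bi-weekly for 3 months/researcher". The components shared by both arms are given once, at first contact.
- **Discussion:** the repeated assessments are called a strength, "which will provide an opportunity to evaluate long-term treatment effects on tobacco abstinence". Slightly earlier, the limits of biochemical verification are acknowledged, "including the inability to confirm long-term abstinence".

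**The concern.** A person who has used no tobacco for 6 months has used none in the last 7 days. The longer claim therefore contains the shorter one, yet the protocol holds the longer claim to the weaker standard of proof. At one visit the same person can be a tobacco user on the primary outcome and continuously abstinent on the secondary one. The reported continuous-abstinence rate could even exceed the verified 7-day rate, which would be hard to explain to a reader.

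The setting makes this more than a matter of tidiness. Intensive-arm participants have had five calls and a run of messages from the person who then asks whether they have quit, and neither side is blinded. The Background criticises earlier research for relying on self-report where biochemical verification was possible. At stake is the credibility of the secondary result that readers will use to judge whether quitting lasted. The primary comparison is not at stake.

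**Working it through.** **1. The two 6-month definitions side by side.**

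| | Primary | Secondary |
|---|---|---|
| Outcome | 7-day point prevalence abstinence | Continuous abstinence |
| Visit | 6 months | 6 months (also 1 and 3) |
| Evidence required | Urinary cotinine | Self-report |
| Urine available at that visit | Yes | Yes, not used |

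Take a participant who reports continuous abstinence and whose urine fails the cotinine rule. Primary outcome: not abstinent. Secondary outcome: abstinent. Nothing in the outcome definitions prevents this pair. The reasoning assumes that continuous abstinence allows no use up to the visit. If the full protocol tolerates occasional lapses, the containment is looser, but a positive result still goes unused.

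**2. What misreporting would do.** Let c1 and c2 be the self-reported continuous-abstinence rates (brief, intensive), and m1 and m2 the share of those claims with a failing cotinine result.

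- Self-reported difference: c2 − c1
- Verified difference: c2(1 − m2) − c1(1 − m1)

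The document gives none of these four quantities. With c1 = 15% and c2 = 25%, both assumed, the self-reported difference is 10 points and the ratio is 25/15 = 1.67.

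| Assumed m1, m2 | Brief verified | Intensive verified | Difference | Ratio |
|---|---|---|---|---|
| 10%, 10% | 15 × 0.90 = 13.5 | 25 × 0.90 = 22.5 | 9.0 | 1.67 |
| 10%, 25% | 13.5 | 25 × 0.75 = 18.75 | 5.25 | 1.39 |
| 25%, 10% | 15 × 0.75 = 11.25 | 22.5 | 11.25 | 2.00 |

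Equal misreporting leaves the ratio alone and trims the difference. Unequal misreporting can move the difference either way. The table shows sensitivity to assumptions and does not estimate the bias in this trial.

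**3. Timing, for interpretation.** Six months is about 26.1 weeks, and the last intensive-arm call is at week 12. So 26.1 − 12 = 14.1 weeks, and 14.1 / 4.345 = 3.2 months. The 6-month visit is about 3 months after intensive support ends and about 6 months after the brief arm's single session.

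**4. Sample size.** The plan's formula with 16.8%, 30.3%, two-sided 0.05 and 80% power gives 151.15, rounded up to 152 per arm. Then 152 × 1.2 = 182.4, rounded up to 183 per arm, which reproduces the stated 366. No continuous-abstinence rate enters, so redefining this secondary outcome changes neither the sample size nor the power.

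**The case against.** The strongest reply is that the protocol labels the measure honestly. Data collection, Secondary outcomes and Table 3 all call it self-reported, it is secondary, and the verified primary can be read beside it. That is true, and it limits the weight of the point. It does not remove the conflicting classifications, since comparing two arm-level rates does not show which claimants failed the urine test.

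A second reply is that cotinine is imperfect. The Discussion says the effect of second-hand smoke could not be ascertained, so a positive result need not disprove a claim. That stands, but the primary outcome already accepts the same error.

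Three stronger readings are tempting and are not supported:

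- **That the trial claims a verified long-term effect it cannot deliver.** The Discussion lists repeated follow-up and cotinine verification as separate strengths. The Objective confines the hypothesis to verified 7-day abstinence at 6 months, and the limit of verification is disclosed. The term long-term is one undefined phrase, and the self-reported series, with relapses recorded at each follow-up, gives some information on durability.
- **That the timing is a design fault.** Both arms are assessed at the same time since enrolment, and Table 1 states the schedule openly. Unequal time since last contact follows from comparing one session with 3 months of support. The 3-month visit falls at about the end of that support, so calling it on-treatment fits poorly.
- **That the self-reported effect would be about halved.** That comes only from assuming 25% against 10% misreporting.

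**Conclusion.** The point holds as an inexpensive improvement to one secondary outcome. Six-month continuous abstinence can be credited to a participant whose urine at the same visit counts against it, in an open-label trial where the treating researcher is also the assessor. This follows from the stated definitions and needs no assumed rate, only that continuous abstinence runs up to the visit.

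The amount and direction of any bias are unknown, because the document gives no rate from which to calculate them. The primary outcome is untouched. When the results are interpreted, the 6-month visit should be described as about 3 months after intensive-arm support ends.

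**What to change.** At 6 months, count a participant as continuously abstinent only if both conditions hold: continuous abstinence is self-reported, and the 6-month urine passes the same cotinine rule as the primary outcome. Count dropouts as tobacco users, as the dropout/withdrawal criteria already provide, and treat an unusable or missing sample exactly as the primary outcome does. Show the self-reported 6-month figure alongside. State that a negative test does not prove abstinence over the whole period. The 1- and 3-month measures stay self-reported, since urine is collected only at 6 months.

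Cost: no new visit, sample or assay. Reported rates will be somewhat lower, and second-hand smoke may misclassify some true abstainers, as it may for the primary outcome. According to Trial status, recruitment was under way, so this would change an outcome definition in a running trial. It should be dated and recorded before the arms are compared.

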### Dissemination of study results

The evidence generated on the effectiveness of tobacco cessation intervention in India’s tertiary care setting will be communicated at scientific meetings and submitted for publication in peer-reviewed journals for more comprehensive readability. Besides, package developed and evaluated from current study will provide evidence for large-scale future research and will provide opportunity to motivate tobacco using patients with better access to behavioral change intervention such as videos, information material, and messages for tobacco cessation. ClinicalTrials.gov record will also be updated regularly.

## Trial status

Recruitment of participants started in December 2020 and is currently ongoing. The study findings are expected to be available in August 2022.
